#### 2.12.5 Analysis of the secondary and exploratory outcomes

For dichotomous outcomes, including the proportion of patients of good functional status (mRS ≤2), the proportion of poor-HRQOL (EQ-5D index score ≤0.5), the proportion of patients with functional independence (BI ≥ 90), the distribution of mRS scores, recurrence rates of stroke, and the proportion of new combined vascular events, a comparison of how patients with these outcomes are distributed among the two groups will be assessed using a chi-square test or Fisher’s exact test and presented as OR estimates and 95% CIs using logistic regression. Moreover, the distribution of functional outcomes on the mRS in both groups will be expressed in histograms. For other secondary outcomes of continuous variable, the changes from baseline to the endpoint of treatment for the above outcomes, including neurological deficit, motor function and cognitive function will be analyzed using the Student’s t test or Wilcoxon rank-sum test where appropriate. For survival data, the Kaplan-Meier method will be used to estimate the survival rate of each group; a survival curve will be drawn, and the log-rank test will be used to evaluate the curative effect. Cox proportional hazards models will be used to calculate hazard ratios (HR) and 95% CIs between the two treatment regimens. The central effect will be set as a random effect in all models. All statistics will be evaluated using two-sided tests, and *p* < 0.05 will be considered statistically significant.

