### 2.4 Efficacy outcomes

The primary outcome will be the proportion of patients with a favorable outcome, which is defined as mRS ≤1 on D90 (Rankin, 1957). The mRS is an ordinal scale ranging from 0 to 6 (Lees et al., 2012), with 0–1 indicating no disability, 2 to 5 indicating disability (increasing from 2 to 5), and 6 indicating death. The secondary outcomes will be as follows: 1) distribution of mRS scores [will be measured on D30 and D90]; 2) proportion of patients with good functional status [defined as mRS score ≤2; will be measured on D30 and D90]; 3) neurological deficit improvement [defined as a change in the National Institute of Health Stroke Scale (NIHSS) score (Brott et al., 1989), ranging from 0 to 42, with higher scores indicating more severe strokes; will be measured at baseline, D30, and D90]; 4) proportion of poor health-related quality of life (poor-HRQOL) [available EuroQol-5D Questionnaire (EQ-5D) data will be used to calculate EQ-5D index scores (Dorman et al., 1997). Poor-HRQOL is defined as an EQ-5D index score ≤0.5 and will be measured on D30 and D90. The EQ-5D index score is measured on a scale between 0 (death) and 1 (full health). The patient’s mobility, self-care ability, daily activities, feelings of pain or discomfort, and feelings of anxiety or depression contribute to EQ-5D. Here, each aspect will be divided into three levels (Rabin and de Charro, 2001): no problems, moderate problems, or extreme problems. The EQ-5D index score (preference-based health status) will be determined using the population-based preference weight values for five dimensions of the scale (Dolan, 1997; Shaw et al., 2005; Liu et al., 2014). This study will use preference weights applicable to the Chinese population (Liu et al., 2014)]; 5) proportion of patients with functional independence [defined as Barthel Index (BI) ≥90 (Mahoney and Barthel, 1965); BI is a conventional scale used to assess the activities of the daily living of stroke patients involving 10 items with a maximum score of 100 points; will be measured on D30 and D90]; 6) changes in motor function [measured by the Fugl–Meyer Motor Scale (FMMS) score (Fugl-Meyer et al., 1975), ranging from 0 to 100, with lower scores indicating poorer motor status; the change from baseline of the FMMS will be measured on D90]; and 7) changes in cognitive function [measured by the Montreal Cognitive Assessment (MoCA) score (Nasreddine et al., 2005), ranging from 0 to 30, with less than 26 indicating cognitive impairment; the change in MoCA from baseline will be measured on D90].

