
### 2.5 Exploratory outcomes

In this trial, the exploratory outcomes will be as follows: 1) In the experimental and control groups, 30 cases will be randomly selected from patients who have had previous intracranial artery stenosis in the past, or at their current admission, to compare changes in blood vessel characteristics and plaques under high-resolution magnetic resonance (HR–MR) between the two groups after 180 days; 2) The magnetic resonance imaging (MRI) diffusion tensor imaging (DTI) anisotropy score, average diffusion rate, and diffusion tensor fiber bundle imaging will be compared between the two groups [30 cases will be randomly selected from each group; will be measured on D180]; 3) The proportion of patients with a good function status [defined as mRS score ≤2] will be measured on D180; 4) The distribution of the mRS scores will be measured on D180; 5) Motor function will be assessed by the FMMS score, which will measure its change from baseline at 180 days; 6) Cognitive function will be assessed by the MoCA score; its change from baseline will be measured on D180; 7) Recurrence rate of stroke [defined as cerebral infarction, cerebral hemorrhage] will be measured on D180; 8) The proportion of new combined vascular events [defined as ischemic stroke, hemorrhagic stroke, myocardial infarction, or vascular death] will be measured on D180.

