#### 2.12.4 Analysis of the primary outcome

The primary outcome, the proportion of patients with favorable outcome in each group, will be compared by the chi-square test. Assessment of the primary effect will involve the analysis of differences in mRS scores between the LSZ treatment and placebo groups using ordinal logistic regression; the results will be expressed as odds ratios (ORs) with 95% confidence intervals (CIs). Both covariate-adjusted analysis and covariate-unadjusted analysis will be performed. Adjusted analyses will incorporate the following covariates: age, sex, baseline National Institutes of Health Stroke Scale (NIHSS) score, TOAST classification. Adjusting for prognostic factors enhances statistical power in clinical trials, which can also correct for imbalances in baseline prognostic variables, reducing data variability (Optimising the Analysis of Stroke Trials (OAST) Collaboration et al., 2009; Kahan et al., 2014).

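### Section 2.12.5 classes the seven-level mRS distribution as a dichotomous outcome, so D30 and D180 have no analysis that uses the order of the scale and D90 has two conflicting methods

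*Protocol article*

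**What the plan says.** Section 2.4 describes the scale: "The mRS is an ordinal scale ranging from 0 to 6". It makes the first secondary outcome the "distribution of mRS scores [will be measured on D30 and D90"]. Section 2.5 adds a third time point as exploratory: "The distribution of the mRS scores will be measured on D180".

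Section 2.12.5 then sets the method. Its list begins "For dichotomous outcomes, including the proportion of patients of good functional status (mRS ≤2") and goes on to "the distribution of mRS scores, recurrence rates of stroke, and the proportion of new combined vascular events". The comparison for everything in the list "will be assessed using a chi-square test or Fisher’s exact test and presented as OR estimates and 95% CIs using logistic regression". A following sentence adds a display: "the distribution of functional outcomes on the mRS in both groups will be expressed in histograms".

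An ordinal model appears once, in section 2.12.4 on the primary outcome, as "analysis of differences in mRS scores between the LSZ treatment and placebo groups using ordinal logistic regression". The primary outcome is itself binary (mRS ≤1 at D90).

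**The concern.** A distribution over seven ordered levels is not a dichotomous outcome, so the assigned method does not fit. It can be read in two ways, and neither gives a shift analysis.

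- As a chi-square or Fisher test on the full 2×7 table, it treats the mRS levels as unordered labels. A move towards recovery, a move towards disability and a scatter across levels can all give the same p value.
- As a binary comparison with a logistic odds ratio, it needs a cut-point. None is stated for this item, and mRS ≤2 is already a separate item in the list.

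Two analysts could follow the section and report different analyses. What is at stake is the first-listed secondary outcome, whose purpose is to pick up movement anywhere on the scale.

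**Working it through.** **1. The sections side by side.**

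| Time point | Status of the mRS distribution | Method in 2.12.5 | Ordinal model in 2.12.4 |
|---|---|---|---|
| D30 | secondary (2.4) | chi-square/Fisher, logistic OR | not linked |
| D90 | secondary (2.4) | chi-square/Fisher, logistic OR | evidently applies, but filed under the binary primary |
| D180 | exploratory (2.5) | chi-square/Fisher, logistic OR | not linked |

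Section 2.12.4 states no time point for the ordinal model. D90 is inferred from its place under the primary outcome.

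**2. The plan's own figure.** Section 2.11 gives no figure for the mRS distribution. It sizes the binary primary at 1,238 in total (60% against 69%, 90% power, two-sided 5%). The usual two-proportion formula gives 2 × 592 = 1,184 without continuity correction and 2 × 614 = 1,228 with it, which is within 1% of 1,238. Dropout inflation is exact: 1,238 / 0.90 = 1,375.6, rounded up to 1,376. I therefore use 1,238 / 2 = 619 per arm.

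**3. The planned effect as an odds ratio.** (0.69/0.31) / (0.60/0.40) = 2.226 / 1.5 = 1.484.

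**4. Order and direction.** Degrees of freedom for a 2×7 table are (2−1)(7−1) = 6. Take an assumed control distribution of 25/35/12/11/9/4/4% for mRS 0 to 6, and shift it by a common odds ratio of 1.484. The expected counts are:

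- control: 155, 217, 74, 68, 56, 25, 25
- LSZ: 205, 222, 63, 53, 41, 17, 17

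Pearson chi-square is 15.11 on 6 df, p = 0.019. Swapping the arms gives 15.11 again, and so does shuffling the seven categories. The statistic cannot tell benefit from harm or from scatter.

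**5. Power.** The inputs are 619 per arm and a control share of 60% with mRS ≤1 (section 2.11). The rest of the control distribution is assumed, because the article gives only that share. Each cumulative odds is multiplied by the common odds ratio to give the LSZ distribution. There were 4,000 simulated trials per scenario, two-sided 5%. The order-using test is the tie-corrected Wilcoxon rank-sum, which stands in for the proportional-odds score test.

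Control distribution 28/32/13/11/9/4/3%:

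| Common OR | mRS ≤1 in LSZ arm | Chi-square, 6 df | Order-using test |
|---|---|---|---|
| 1.25 | 65.2% | 31% | 60% |
| 1.35 | 66.9% | 56% | 84% |
| 1.48 (planned) | 69.0% | 84% | 97% |

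The second column follows from 1.5 × OR / (1 + 1.5 × OR); for example, 1.875 / 2.875 = 65.2%. Both tests reject about 5% of the time under no effect.

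**6. Sensitivity to the assumed distribution.** Three other control distributions, all with 60% at mRS ≤1 (25/35/12/11/9/4/4, 20/40/15/10/8/3/4 and 35/25/10/10/10/5/5%), gave:

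| Common OR | Chi-square, 6 df | Order-using test | mRS ≤1 split |
|---|---|---|---|
| 1.3 | 44% | 72–73% | 60–62% |
| 1.484 | 83–85% | 97% | 91–92% |

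In these scenarios the 6-df test also has less power than the simple mRS ≤1 split.

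**The case against.** The strongest reply is that the plan already contains an order-using analysis. Section 2.12.4 specifies ordinal logistic regression of mRS scores, adjusted and unadjusted, with odds ratios and confidence intervals. On that view the entry in 2.12.5 is a slip in a list in a condensed article. Much of this stands for D90, and a reader who inferred that the trial has no shift analysis at all would be wrong. It does not settle the matter. Nothing ties that model to D30 or D180, and at D90 the two sections give different methods for the same data. Reading the logistic regression in 2.12.5 as ordinal is strained, because the sentence governs dichotomous outcomes and 2.12.4 says ordinal when it means it.

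A reader might also infer that the plan could never show the direction of a shift. That goes too far. The lack of direction belongs to the chi-square or Fisher test. The histograms show direction descriptively, and a binary odds ratio has a direction at its one, unstated cut.

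Nor can it be said that the planned dichotomies make a distribution analysis redundant. A seven-level scale has six cuts. The mRS ≤1 and ≤2 splits are two of them, and mRS ≤1 is defined only at D90.

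Finally, the power figures all assume a proportional shift, which favours the order-using test, and the widest gaps lie below the planned effect. Both limits are fair. No non-proportional scenario was run.

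**Conclusion.** The point holds as a misclassification. Section 2.12.5 assigns the mRS distribution a method for dichotomous outcomes, against the ordinal definition in 2.4 and out of step with 2.12.4. As written, D30 and D180 have no order-using analysis, and D90 has two methods without a rule for which one belongs to the secondary outcome.

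If the 2×7 chi-square is used, the cost is about 13 percentage points of power at the planned effect (84% against 97%) and about 29 points at an odds ratio of 1.25 (31% against 60%). These sizes rest on 619 evaluable patients per arm, an assumed mRS distribution and a proportional shift, with the D90 control share applied throughout. They are indicative for D30 and D180. For D90 the ordinal model in 2.12.4 mitigates the loss.

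Neither the primary mRS ≤1 comparison nor its sample size is affected. The change should be made, but it does not threaten the trial's main conclusion.

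**What to change.** 1. In 2.12.5, remove the mRS distribution from the list of dichotomous outcomes.
2. Specify ordinal (proportional-odds) logistic regression for it at D30, D90 and D180, with the random centre effect that 2.12.5 already asks for in all models, reported as a common odds ratio with 95% CI.
3. In 2.12.4, state that the ordinal model at D90 serves this secondary outcome and not the binary primary.
4. Keep the histograms as the display.
5. If a rank-sum test is wanted, pre-specify it as a sensitivity analysis. It should not replace the model when proportional odds looks doubtful: that would be a data-driven switch without a criterion, and it would drop the centre effect and give no odds ratio.

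The cost is a sentence in each of two sections. No new data, visits or patients are needed.

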### 2.11 Sample size calculations and interim analysis

The 90-days mRS distribution of the eligible population in The Third China National Stroke Registry (CNSR-Ⅲ) indicates that the proportion of mRS ≤1 is 60.42% (Wang et al., 2019). This study assumes that the proportion of patients with mRS ≤1 in the control group will be 60%, and the proportion of patients with mRS ≤1 in the experimental group will be increased by approximately 15% for a proportion of 69%. According to this assumption and calculations using PASS 11.0 software (NCSS, LLC, East Kaysville, UT, United States), a total sample size of 1,238 in the two groups can achieve 90% power and rule out two-sided type I errors of 5% to detect a superiority margin difference of 5% in this two-arm trial, with an allocation ratio of 1:1. With an estimated loss-to-follow-up rate of 10%, a total of 1,376 participants will be recruited. An interim analysis will be performed when the 50% of recruited patients (619) complete the study. The interim analysis will allow the DSMB to decide whether to continue or terminate the study. Based on the existing data and the expected final sample size, if this study is not expected to obtain efficacious results, the study will be terminated immediately in the current period. For evaluation of the effectiveness of the research, if the research has met the validity standard and meets the requirements of the inspection level, the study can be terminated early. The study will continue if the estimated efficacy is expected to be achieved by the end of the study. If the estimates of the primary outcome in the study (blinded) differ significantly from the actual values, the final sample size allows for appropriate adjustments at the interim analysis.

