### 2.12 Statistical analysis plan

#### 2.12.1 Full analysis set

Statistical analysis will be conducted by a third-party statistical unit using SAS v9.4 software (SAS Institute, Inc.). The full analysis set (FAS) will be the data set as close as possible to the ideal set of subjects in compliance with the intention-to-treat principle, and all subjects who are randomized into the group and have more than one medication record and evaluation of its efficacy will be included in the FAS. Missing data will be imputed using the last observation carried forward (LOCF) method if there are efficacy values after randomization. The FAS will be used for primary efficacy analysis in this study, and all efficacy variables will be analyzed using the FAS.

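### Stroke recurrence and combined vascular events at D180 are assigned to tests that cannot censor, while the planned survival methods are assigned to no named outcome

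*Protocol article*

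**What the plan says.** Section 2.5 of the protocol article defines two exploratory event outcomes: "Recurrence rate of stroke [defined as cerebral infarction, cerebral hemorrhage] will be measured on D180" and "The proportion of new combined vascular events [defined as ischemic stroke, hemorrhagic stroke, myocardial infarction, or vascular death] will be measured on D180". Section 2.12.5 then includes them among the dichotomous outcomes ("recurrence rates of stroke, and the proportion of new combined vascular events, a comparison of how patients with these outcomes are distributed"), to be compared by "chi-square test or Fisher’s exact test and presented as OR estimates and 95% CIs using logistic regression".

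Further on, the same section states: "For survival data, the Kaplan-Meier method will be used to estimate the survival rate of each group". It adds a log-rank test, and "Cox proportional hazards models will be used to calculate hazard ratios (HR) and 95% CIs between the two treatment regimens". No outcome is named for these methods, and none in sections 2.4 or 2.5 is defined as a time to event.

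Two other provisions bear on patients lost early. Section 2.12.1 applies the full analysis set to all efficacy variables and says: "Missing data will be imputed using the last observation carried forward (LOCF) method if there are efficacy values after randomization". Section 2.11 says: "With an estimated loss-to-follow-up rate of 10%, a total of 1,376 participants will be recruited".

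**The concern.** Both outcomes are events that accrue over 180 days. A patient last seen event-free on day 60 has no known yes/no status at D180. A chi-square test or logistic model must either give that patient a value or leave the patient out. A survival method uses the 60 days of follow-up and censors the patient there. The plan contains the suitable methods but attaches the unsuitable ones to these two outcomes by name.

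At stake are the reported D180 event rates and, if loss differs between arms, the comparison itself. The direction of the error depends on a scoring choice that the article does not make. It is better fixed before unblinding, given that the article's stated purpose is to prevent selective analysis.

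**Working it through.** **The plan's own figure.** 1,238 / (1 - 0.10) = 1,375.6, rounded up to 1,376, or 688 per arm. The 10% therefore corresponds to about 138 patients, about 69 per arm. It is a sample-size allowance for the D90 primary outcome. The article gives no loss rate for D180, so 10% is used below as an assumption.

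**Other assumptions.** The article gives no D180 event rate. I take a true risk R = 8% in both arms (range 5-12%), constant hazard and non-informative loss of a fraction d. Two loss patterns are used: all loss just after D30, and loss spread evenly over 180 days.

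**Risk already observed at the time of loss (F).**
- Loss just after D30: F = 1 - (1 - R)^(30/180) = 1 - 0.92^(1/6) = 0.0138.
- Even loss: F = 1 - R / (-ln(1 - R)) = 1 - 0.08/0.0834 = 0.0406.

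**Lost patients counted event-free.** Reported risk = (1 - d)R + dF.
- Loss just after D30, d = 10%: 0.9 × 0.08 + 0.1 × 0.0138 = 0.0734, so 8.0% reads as 7.3% (5% as 4.6%, 12% as 11.0%).
- Even loss: 0.9 × 0.08 + 0.1 × 0.0406 = 0.0761, so 8.0% reads as 7.6%.

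**Lost event-free patients dropped, earlier events kept.** Divide the above by 1 - d(1 - F).
- Loss just after D30: 0.0734 / 0.9014 = 0.0814, about 8.1%.
- Even loss: 0.0761 / 0.9041 = 0.0841, about 8.4%.

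Under the same assumptions, Kaplan-Meier with censoring recovers 8.0% in every case.

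**Between-arm comparison, equal loss of 10%.** With no true effect the odds ratio stays at 1.00. With a hazard ratio of 0.8 and even loss, the true odds ratio is 0.793. It reads 0.794 if lost patients count as event-free and 0.793 if they are dropped.

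**Between-arm comparison, unequal loss, no true effect, R = 8%.** Rejection rates use the normal approximation with 688 per arm.

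| Loss, placebo / LSZ | Pattern | Scoring | Risk, placebo / LSZ | OR | Two-sided rejection |
|---|---|---|---|---|---|
| 5% / 15% | just after D30 | event-free | 7.67% / 7.01% | 0.91 | 7.6% |
| 5% / 15% | even | event-free | 7.80% / 7.41% | 0.945 | 5.9% |
| 7% / 13% | just after D30 | event-free | 7.54% / 7.14% | 0.943 | 5.9% |
| 7% / 13% | even | event-free | 7.72% / 7.49% | 0.967 | 5.3% |
| 5% / 15% | just after D30 | dropped | 8.07% / 8.22% | 1.02 | not computed |
| 5% / 15% | even | dropped | 8.20% / 8.65% | 1.06 | not computed |

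For the first row, the rejection rate runs from 6.6% at a 5% risk to 9.0% at a 12% risk. Reversing the 5/15 split under even loss gives about 1.06 (event-free) or 0.94 (dropped).

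**The case against.** The best defence is that the Kaplan-Meier and Cox sentences were meant for these two outcomes, alongside the D180 proportion. Section 2.12.5 covers only secondary and exploratory outcomes, and nothing else among them looks like survival data. This may well be the intention, so it cannot be said that the plan rules out censoring. But each outcome would then have both an odds ratio and a hazard ratio at the same 5% level with neither leading, and the text would need the same edit. Section 2.12.6 plans Cox models for most safety endpoints. That may cover overlapping events, but not these two outcomes as defined.

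A reader might infer that the plan counts lost patients as event-free or drops them. The documents fix neither. Section 2.5 places both outcomes at D180 and defines no D30 or D90 value, so whether the LOCF rule has anything to carry forward is open. Nor does the text support saying that event rates will be understated or that the arm losing more patients will look protected. Dropping those patients reverses both.

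A reader might also take 10% as the plan's estimate of loss by D180. It is not stated as that.

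Finally, both outcomes are exploratory, a D180 proportion with an odds ratio is a recognised summary, and nothing in the article suggests unequal loss in a trial with matched placebo. These points stand and limit the severity. They do not make the stated method the better one.

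**Conclusion.** The point holds at low severity. Two incident-event outcomes are assigned by name to methods that cannot censor, and the suitable methods in the same section are assigned to nothing. Under an assumed 8% risk and 10% loss per arm, the D180 rate would be misstated by roughly 0.1 to 0.7 percentage points, in a direction set by an unstated scoring rule.

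The comparison between arms is nearly unaffected by equal, non-informative loss. The odds ratio of 0.91 and the 7.6% rejection rate need all loss just after D30, a threefold difference in loss between arms, and event-free scoring. They are the upper end of the scenarios examined, not an expectation. The calculations do not cover loss related to event risk, which censoring would not fully repair either.

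**What to change.** In section 2.12.5, move stroke recurrence and new combined vascular events from the dichotomous list to the survival-data sentence. Define each as time from randomization to first event, censored at last contact or D180. Make the log-rank test and the Cox model already planned, with its random centre effect, the lead analysis. State that LOCF does not apply to event outcomes. Report D180 cumulative incidence, treating deaths outside the outcome as a competing event. At assumed death risks of 2-8% this differs from one minus Kaplan-Meier by at most about 0.5 points, so it is a safeguard.

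The cost is a change of wording. The lead effect measure for two exploratory outcomes becomes a hazard ratio instead of an odds ratio. Event dates must be taken from the adverse event records, which section 2.7 says are made whenever events occur.

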## 2 Methods and design

### 2.1 Study design and patient selection

The LONGAN trial is a prospective, multicenter, randomized, placebo-controlled, double-blind, parallel-group, superiority trial that enrolls patients from stroke and rehabilitation units in China. This study will be conducted at 15 sites across China. The primary objective of the trial is to test the hypothesis that LSZ capsule is superior to the placebo for increasing the proportion of favorable functional status, defined as a modified Rankin Scale (mRS) score ≤1 at 90 days. The secondary objective is the assessment of any other benefits or harms from the end of the treatment period up to 180 days after the stroke. Participants will be followed up at 30, 90 and 180 days after randomization (D30, D90 and D180, respectively) to collect efficacy and safety outcomes in person. Patient enrollment will begin in May 2022 and end in June 2023. Figure 1 presents a schematic diagram of the patient timeline. The trial was approved by the institutional review board of Dongzhimen Hospital, Beijing University of Chinese Medicine, Beijing, China and registered in public clinical trial database (No. 2021DZMEC-198-02; ClinicalTrials.gov Identifier NCT 05277311). We described this study protocol according to the SPIRIT 2013 Statement, and the complete checklist is available.

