### 2.2 Randomization, allocation, and blinding

Eligible patients who consent to participate will be assigned to the LSZ capsule experimental or control group at a 1:1 ratio using permuted block randomization stratified according to medical centers. The randomization program will be generated by an independent statistician using SAS software v9.4 (SAS Institute, Inc.; Cary, NC, United States) and stored in sealed, sequential, opaque envelopes. The site pharmacist will retain these envelopes, which will be assigned in the order specified by the statistician.

At randomization, study medications will be packaged into a large box containing LSZ capsules or LSZ placebo capsules. When the patient is discharged, the trial medication will be continued and documented on the discharge summary and on the patient’s list of ongoing medications. At 30 days after randomization, patients will be instructed to bring partial empty boxes to this follow-up. Patients who stop taking the allocated treatment early will be followed up, and their data will be included in the primary analyses. The reason for stopping the treatment prematurely, e.g., a SAE, will be recorded in the patient’s electronic case report form (CRF).

Active and placebo capsules with identical appearances, colors, and flavors will be prepared by Buchang Pharmaceutical Co, Ltd. The placebo capsules are visually identical to the LSZ capsules, even when broken open. In the study, each patient’s medications will be prepared as a unit-dose kit according to the predetermined randomization schedule. The site pharmacies will not disclose the randomization assignments unless information is required for patient treatment in exceptional circumstances. The clinical center pharmacist will be unblinded to the treatment, but all investigators, participants, caregivers, and data analysts will be blinded to treatment assignments throughout the trial until the blind codes are revealed. Investigators can request emergency unblinding in cases of serious adverse events (SAEs) suspected to be associated with the investigational medicine.

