### 2.7 Follow-up procedures

The study will consist of four visits, including time of randomization (baseline) and 30, 90, and 180 days after randomization. At baseline, we will evaluate demographic characteristics; routine laboratory test results; computed tomography (CT)/MRI results; electrocardiogram (ECG) results; and NIHSS, Alberta Stroke Program Early CT Score (ASPECTS) (Barber et al., 2000), mRS, FMMS, MoCA, BI and EQ-5D scores. Stroke types will be classified according to the trial of ORG 10172 in acute stroke treatment (TOAST) criteria. At 30, 90, and 180 days after randomization, we will perform assessments using the mRS, NIHSS, FMMS, MoCA, BI and EQ-5D scores. Vital signs and physical examination findings will be recorded at both baseline and 90 days. Finally, medication use for comorbidities and adverse events information will be recorded at whenever they occur during the trial.

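### Changes in NIHSS, FMMS and MoCA are assigned to unadjusted two-sample tests that use neither the baseline score as a covariate nor centre: an avoidable loss of precision, not of validity

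*Protocol article*

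**What the plan says.** Section 2.12.5 takes "the changes from baseline to the endpoint of treatment for the above outcomes, including neurological deficit, motor function and cognitive function" and assigns them to Student's "t test or Wilcoxon rank-sum test where appropriate". It names no covariate for them. Later in the same section comes a general rule: "The central effect will be set as a random effect in all models".

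Three other places bear on this:

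- **Section 2.7** lists the scores taken at baseline as "NIHSS, Alberta Stroke Program Early CT Score (ASPECTS) (Barber et al., 2000), mRS, FMMS, MoCA, BI and EQ-5D scores". The baseline value of each of the three scales will therefore be in hand.
- **Section 2.2** specifies "permuted block randomization stratified according to medical centers", and section 2.1 gives the number of centres: "This study will be conducted at 15 sites across China".
- **Section 2.12.4**, under the primary outcome, says: "Adjusted analyses will incorporate the following covariates: age, sex, baseline National Institutes of Health Stroke Scale (NIHSS) score, TOAST classification". It justifies this by the gain in power and the correction of baseline imbalance.

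By sections 2.4 and 2.5, the outcomes concerned are NIHSS change (D30 and D90), FMMS and MoCA change at D90 (secondary), and FMMS and MoCA change at D180 (exploratory).

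**The concern.** A change score uses the baseline value only by subtraction, which fixes the slope of follow-up on baseline at 1. Wherever the true slope differs from 1, part of the baseline variation stays in the comparison as noise, and regression on the baseline value would remove it. The plan accepts this argument for the primary outcome and does not carry it to the outcomes for which a same-scale baseline exists.

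There is also an internal mismatch. A t test or a rank-sum test is not a model with a random effect, and no model is named for these three outcomes, so the rule on centre cannot be carried out for them.

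At stake are wider confidence intervals and lower power for the neurological, motor and cognitive outcomes than the same data allow.

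**Working it through.** **Design figure in the article.** The only computable one is the sample size for the binary primary outcome (section 2.11): 60% against 69%, two-sided 5%, 90% power, 1:1. The standard two-proportion formula gives 614 per arm, or 1,228, with continuity correction (592 per arm, or 1,184, without), against 1,238 stated. Then 1,238/0.90 = 1,376, as stated. This point leaves that figure untouched. No SD, correlation, effect size or power is given for NIHSS, FMMS or MoCA.

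**Formulas.** Let r be the correlation of baseline with follow-up and k the follow-up SD divided by the baseline SD. Both are assumptions. In units of the baseline variance, and up to a common factor, the variance of the treatment effect is:

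- change score: 1 + k² − 2rk
- ANCOVA on baseline: k²(1 − r²)

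The difference is (1 − rk)². It is never negative, and it is zero only when the slope rk equals 1. So in large samples ANCOVA is never less precise.

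**Equal SDs (k = 1).** The ratio of ANCOVA to change-score variance reduces to (1 + r)/2. The CI narrows by 1 − √ratio. If the t test had 80% power, ANCOVA would have Φ((1.96 + 0.84)/√ratio − 1.96).

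| r | Variance ratio | CI narrower by | ANCOVA power if t test has 80% |
|---|---|---|---|
| 0.3 | 0.65 | 19% | 93.5% |
| 0.5 | 0.75 | 13% | 90% |
| 0.7 | 0.85 | 8% | 86% |
| 0.9 | 0.95 | 2.5% | 82% |

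**Unequal SDs.** Variance ratio k²(1 − r²)/(1 + k² − 2rk):

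| k | r = 0.5 | r = 0.7 |
|---|---|---|
| 0.75 | 0.52 | 0.56 |
| 1.00 | 0.75 | 0.85 |
| 1.25 | 0.89 | 0.98 |
| 1.50 | 0.96 | 1.00 |

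For example, k = 1.5 and r = 0.7 gives 2.25 × 0.51/(3.25 − 2.10) = 1.1475/1.15 = 0.998.

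**Simulation.** Settings: 1,238 patients, 15 centres, allocation balanced within centre, normal data, equal SDs, 1,500 runs per scenario. Centre was entered as fixed indicators, as a stand-in for the random effect. Type I error lay between 0.041 and 0.053 for every method. Power:

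| r | Centre ICC (assumed) | t test | Rank-sum | ANCOVA | ANCOVA + centre |
|---|---|---|---|---|---|
| 0.3 | 0 | 0.79 | 0.78 | 0.93 | 0.93 |
| 0.5 | 0 | 0.81 | 0.79 | 0.90 | 0.90 |
| 0.7 | 0 | 0.80 | 0.78 | 0.85 | 0.85 |
| 0.7 | 0.05 | 0.83 | 0.80 | 0.88 | 0.89 |
| 0.9 | 0 | 0.80 | 0.78 | 0.82 | 0.82 |

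Nearly all of the gain comes from the baseline value. Centre adds about 0 to 1 percentage point.

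**The case against.** **It is only an efficiency preference.** This stands. The planned tests are legitimate, hold their level, and touch no primary result. The primary outcome already has an adjusted analysis.

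**The article condenses a fuller plan.** The introduction says it summarizes the protocol and SAP for the primary analysis, and nothing rules out further adjusted analyses elsewhere. That limits the point but does not remove it: the article does not leave the method open, it names it.

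**The size is unknown.** This also stands. A reader might take the equal-SD result at r of 0.5 to 0.7 as a fixed 15–25% saving. The documents do not support that. Equal SDs are doubtful for NIHSS, where entry is limited to 4–15 while the scale runs from 0 to 42, and at k = 1.5 the gain nearly disappears. The variance formula also does not cover the rank-sum option. Nor could any such saving change recruitment, since the sample size rests on the binary primary outcome.

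**Bias.** A reader might infer that chance imbalance in baseline severity biases the comparison as a separate fault. Over randomization it does not: the imbalance is already part of the change-score variance, so this is the same loss seen conditionally. With 619 per arm, one standard error of baseline imbalance is √(2/619) = 0.057 SD. At equal SDs the change score passes on 1 − r of it, or 0.017 to 0.028 SD for r of 0.7 to 0.5. Nor is change always negatively correlated with baseline. That requires rk < 1, and at r = 0.7 and k = 1.5, rk = 1.05.

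**Centre.** The rule on random centre effects shows an intention to adjust. It cannot be met by the named tests, but the cost in power is small.

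**Conclusion.** The point holds as an avoidable loss of efficiency, confined to secondary and exploratory outcomes. The named tests leave the baseline value unused as a covariate and cannot follow the article's own rule on centre, although the data are collected and section 2.12.4 makes the case for adjustment.

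The size rests on assumed r and k. The variance ratio is 0.65 to 0.95 with equal SDs and r from 0.3 to 0.9. It is about 0.52 to 1.00 for r from 0.5 to 0.7 and k from 0.75 to 1.5. The gain may therefore be large or nil, but asymptotically it is never a loss. The change is recommended because it costs almost nothing. The planned analysis would not be invalid without it.

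**What to change.** In section 2.12.5, or in the full SAP, before unblinding:

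1. Name as the main analysis of NIHSS (D30, D90), FMMS (D90) and MoCA (D90) a linear mixed model of the follow-up score, or equivalently the change, on treatment and the baseline value of the same scale, with centre as a random effect.
2. Add age, sex and TOAST class to match section 2.12.4. Add baseline NIHSS for FMMS and MoCA only, because for NIHSS it is already in the model.
3. Report the adjusted mean difference with its 95% CI.
4. Keep the rank-sum test as a pre-specified sensitivity analysis, not as an alternative chosen after seeing the data.
5. Use the same model for FMMS and MoCA at D180.

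The cost is plan wording and a few lines of code. No new data, visits or patients are needed.
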